#### Audits

A final audit is scheduled in the participating centers. These audits are carried out to check whether the conduct of the study is in accordance with ICH-GCP regulations. Independence from the trial personnel involved in HASTA is guaranteed for every auditor. Investigators have agreed to give auditors free access to all relevant documents. Based on the results of these audits the two monitoring strategies will be compared.

#### Assessment of safety

According to ICH-GCP the term "adverse event" covers any clinically relevant sign, symptom, syndrome, illness that appears or worsens in a subject during the period of observation in the clinical trial and that may impair the well-being of the subject.

Adverse events fall into the categories non-serious and serious. Non-serious adverse events will not be documented in HASTA trial. The following conditions and treatments are expected after the initial operation and will therefore not be classified as AE: pain, nausea, hyper-/hypotension, blood sugar problems, electrolyte imbalances and other lab values out of normal range, if they are not exceeding the duration and extent that can be expected after such an operation.

However, all endpoint relevant complications (i.e. bowel obstruction, wound infection, anastomotic leakage of the ileostomy closure, re-operation) are explicitly being asked for and documented in the CRF as endpoint (not as adverse events). Any other complications that are considered as clinically relevant by the investigator should be documented in free text.

From the day the subject has signed informed consent until the regular end of trial at 12 months follow-up or until premature withdrawal of the patient, all serious adverse events (SAE) must be documented on a "serious adverse event form" available in the investigator site file. Serious adverse events have to be reported by the attending physician to the principal investigator within 5 days after the SAE becomes known.

It is the responsibility of the principal investigator to register all SAEs and to check incoming SAEs as to completeness, correctness and plausibility.

In case of any irregularities for example concerning the frequency or type of SAE reported the principal investigator will inform the members of the Independent Data Safety Monitoring Board (DSMB) without delay. At least once every 12 months, the DSMB will receive a written safety report. The members of the DSMB then report the result of the benefit/risk assessment to the principal investigator and will give appropriate recommendations concerning the continuation of the trial.

Analysis of safety related data is performed with respect to frequency of SAE in both treatment groups and frequency of SAE stratified by causality.

### Statistical methods

#### Analysis

##### Analysis sets

Each patient's allocation to the different analysis populations (full analysis set (FAS) according to the intention-to-treat (ITT) principle, per protocol (PP) analysis set, safety analysis set) will be defined prior to the analysis. The allocation will be documented in the statistical analysis plan. During the data review, deviations from the protocol will be assessed as „minor" or „major". Major deviations from the protocol will lead to the exclusion of a patient from the PP analysis set.

##### Confirmatory analysis

The null-hypothesis is assessed by testing the intervention effect in a logistic regression model that takes into account the covariates "intervention" (hand-suture/stapler) and "skill of surgeon" (board certificate yes/no). Due to the high number of targeted centers (approximately 20), the variable "center" for which randomization was stratified is not planned to be additionally included in the model. A two-sided type I error rate of will be applied.

Confirmatory analysis will be primarily based on the FAS which is consistent with the intention-to-treat (ITT) principle by including all patients who were randomized to the two groups. This approach reflects the idea that the study should match as close as possible to the conditions in clinical practice.

If a patient discontinues from the study prematurely, missing data with respect to the primary outcome variable will be replaced by ICA-r method described by Higgins et al. (2008) [12].

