### Preliminary data

One randomized controlled trial (RCT) including 141 patients over 6 years has compared hand-sutured and stapled anastomosis for closure of loop ileostomy so far [9]. The results of this trial have shown a significantly higher rate of postoperative bowel obstruction (14% versus 3%, p = 0.0168) for patients who received hand-sutured anastomosis. However, there are severe methodological issues which impair the interpretation of this trial. First, the trial included a heterogeneous group of patients with many different underlying benign and malignant diseases. Second, it was performed in a single-center setting with only a low number of surgeons performing the investigated techniques. Therefore, the results reflect the situation of loop ileostomy closure at this institution rather than practice in general. Third, results of this trial are probably biased by learning curve effects of participating surgeons [10]. The authors report that two-thirds of bowel obstructions observed in the trial occurred in the first half of the study. In addition, all patients requiring re-operations had initial closure of the loop ileostomy performed by senior registrars (as opposed to consultant surgeons). Due to the methodological and clinical limitations of this trial a multi-center pragmatic trial is needed to confirm the observed findings.

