### Sample size

The prior assumptions for sample size calculation are based on the results of Hasegawa et al. (2000) ([9]) and assume prevalence rates with respect to the primary endpoint of 3% in the stapler group and 14% in the hand-suture group. To detect this difference with the two-sided chi-square test at a type I error rate of (two-sided) with power, a sample size of n = 133 evaluable patients (treatment and follow up according to the protocol) per group is necessary. It can be expected that taking into account the covariate "skill of surgeon" in the analysis will increase the power as compared to the chi-square test. The drop out rate within one month after index operation is expected to be about 20% overall. Therefore, another total of 68 patients have to be randomized to obtain the required number of evaluable patients. The total sample size to be randomized is therefore 334 patients.

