### Randomization and blinding

The randomization numbers will be allocated to the two groups in balanced permuted blocks and stratified by center using the web-based software "Randomizer" provided by the Institute of Medical Informatics, Statistics and Documentation of the Medical University of Graz (http://www.randomizer.at). This software allows choosing different randomization methods as well as different sets of parameters for the chosen method.

To avoid any potential of predicting the group allocation of future patients, the block length is fixed in a separate document that is withheld from the study site. In addition, persons with the right to randomize with the software described above do not have the right to read or edit the randomization design chosen within the software. The software stores the result of randomization and patient characteristics as well as the name of the person who randomized and the randomization date in a separate file, and only authorized persons can download this file. Patients are randomized the day before or on the day the surgical intervention is performed.

Patients are not blinded and blinding of the surgeon is unfeasible. Typical symptoms for the primary outcome, bowel obstruction, like productive vomiting, gastric tube placement, severe constipation are detected during regular patient care and documented in the medical record. Assessment according to trial criteria is done by investigators.

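### The confirmatory model adjusts for the surgeon's board-certificate status, which the article does not fix before allocation; adjustment could bias the treatment effect if staffing follows both arm and patient difficulty.

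*Protocol article*

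**What the plan says.** All references are to the Protocol article.

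- **Confirmatory analysis.** The null hypothesis is assessed by "testing the intervention effect in a logistic regression model that takes into account the covariates" intervention and skill of surgeon, coded "board certificate yes/no". Center is deliberately left out, so skill is the only adjustment covariate.
- **Randomization and blinding.** "Patients are randomized the day before or on the day the surgical intervention is performed". Randomisation is stratified by center only, and neither patient nor surgeon is blinded.
- **Table 1.** Randomisation and surgery share visit 2; baseline data belong to visit 1.
- **Sample size.** The covariate is mentioned only as something expected to raise power over the chi-square test.
- **Preliminary data.** In the earlier single-center trial, all patients who needed re-operation "had initial closure of the loop ileostomy performed by senior registrars (as opposed to consultant surgeons". The protocol therefore regards operator grade as relevant to outcome.

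No section says that the operator, or the operator's grade, is fixed or recorded before the allocation is shown.

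**The concern.** Adjusting for a prognostic factor is safe when its value cannot depend on the allocation. Here it may. A department that learns the arm up to a day ahead could assign a certified surgeon more readily to one technique. The two techniques are also constrained differently: the stapled anastomosis is prescribed, while hand-suture may follow local habit (Treatment description).

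If certified surgeons also take the harder cases, patients of certified surgeons in one arm are no longer comparable with patients of certified surgeons in the other. A model that compares arms within grade then compares groups of unequal difficulty, although the arms as randomised are balanced. At stake are the validity of the single confirmatory test and the interpretation of its odds ratio.

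**Working it through.** **1. The plan's own figure.** The inputs are 14% and 3% ("assume prevalence rates with respect to the primary endpoint of 3% in the stapler group and 14% in the hand-suture group"). Alpha and power are not legible in the available text; I assume two-sided 0.05 and 0.90. With mean rate (0.14 + 0.03)/2 = 0.085:

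n = [1.960·√(2·0.085·0.915) + 1.282·√(0.14·0.86 + 0.03·0.97)]² / 0.11² = (0.773 + 0.496)² / 0.0121 ≈ 133 per group.

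This matches "a sample size of n = 133 evaluable patients". With 20% dropout, 133/0.8 = 166.25, rounded up to 167 per arm, or 334. The figure comes from the unadjusted test and does not depend on the skill covariate.

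**2. Assumed inputs for the bias check** (none is in the article). 334 patients, 167 per arm, all analysed; no technique effect; overall event rate 8.5% (the mean of the two planning rates); 30% difficult patients with odds ratio 3 for obstruction; at first, no effect of grade itself. The event rates are then 5.6% for easy and 15.2% for difficult patients (0.7·5.6% + 0.3·15.2% ≈ 8.5%). Odds ratios are hand-suture versus stapler.

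**3. Extreme steering, step by step.** Certified surgeons do all difficult cases in both arms, and 71% (hand-suture) or 14% (stapler) of easy cases.

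- Certified share: hand-suture 0.7·0.71 + 0.3 = 79.7%; stapler 0.7·0.14 + 0.3 = 39.8%.
- Difficult among certified: 0.3/0.797 = 37.6% versus 0.3/0.398 = 75.4%.
- Event rate among certified: 0.376·15.2% + 0.624·5.6% ≈ 9.2% versus 0.754·15.2% + 0.246·5.6% ≈ 12.8%. The odds ratio is about 0.69.
- Uncertified surgeons have only easy cases in both arms: 5.6% versus 5.6%, odds ratio 1.00.

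The logistic model pools these to 0.75. Without skill the odds ratio is exactly 1.00.

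**4. Range under no technique effect and no grade effect** (large-sample logistic fit, Wald test at 334)

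| Certified, easy/difficult: hand-suture; stapler | Certified share | Adjusted OR | Type I error, adjusted | Unadjusted OR |
|---|---|---|---|---|
| 71/100%; 14/100% | 80% vs 40% | 0.75 | 10.5% | 1.00 |
| 60/90%; 30/90% | 69% vs 48% | 0.90 | 5.8% | 1.00 |
| 55/70%; 45/70% | 59.5% vs 52.5% | 0.985 | 5.0% | 1.00 |
| Same in both arms | equal | 1.00 | 5.0% | 1.00 |

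A simulation of 3,000 trials gave type I errors of 9.8%, 5.4% and 4.3% for the first three rows. A separate calculation with 50% difficult patients, difficulty odds ratios of 2 to 6 and other steering patterns gave adjusted odds ratios of 0.76-0.88 (strong), 0.86-0.93 (moderate) and 0.98-0.99 (mild).

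**5. Power at 3% versus 14%** (simulated, all 334 analysed). Without skill it is about 96%. With skill it is about 82% in the first row and 93% in the second. Part of this loss is not bias: if grade depends on arm only (80% versus 40%), power with skill is about 92%, simply because the covariate is correlated with the arm.

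**6. When grade does affect outcome.** Let certified surgeons have odds ratios of 0.5 or 0.33 for obstruction.

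- Grade depends on arm only (80% versus 40%): adjusted OR 1.00; unadjusted OR 0.76 or 0.64.
- Extreme joint steering as in step 3: adjusted OR 0.79 or 0.81; unadjusted OR 0.81 or 0.71.

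So the model without skill stays at 1.00 only when grade has no effect of its own. Otherwise it measures technique together with the staffing that the technique attracts.

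**The case against.** The strongest objection is that the point rests on silence in a condensed article. The full protocol or case report form may name the operator beforehand, and nothing shows that operators are chosen by arm. Bias also needs two dependencies at once, on arm and on patient risk, and the documents establish neither. The Discussion gives reasons against strong steering: local hand-suture technique was allowed to avoid learning curves, and the stapled technique was taught with laboratory practice. All of this stands and limits the claim to an open risk. It does not dispose of it, because the article itself fixes the confirmatory model and its covariate, and its stated timing leaves room for the covariate to follow the allocation.

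A reader might infer that even modest selection of operators by arm distorts the result. The figures do not support that: a 7-point shift leaves 0.985 and a type I error of about 5%. A reader might also infer that the confirmatory effect has lost the protection of randomisation, or that the model without skill is simply the correct one. The first would need evidence of arm-dependent staffing, which the article does not contain. The second ignores step 6: if grade matters and depends on arm only, the adjusted model recovers the comparison of techniques at equal skill and the unadjusted one does not.

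**Conclusion.** The point holds as a design weakness with conditional consequences. The sole adjustment covariate may be a post-randomisation variable, and adjusting for the actual operator's grade can bias the confirmatory odds ratio if staffing depends on both arm and difficulty. Under the stated assumptions the null odds ratio is about 0.75 (type I error about 10-11%) with extreme steering, about 0.90 (about 6%) with a 21-point shift, and practically 1 with small shifts. Reversing the steering reverses the direction. No bias has been shown to exist, and the sample size is unaffected.

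**What to change.** 1. Add a mandatory field to the web randomisation form for the planned operator's board-certificate status, completed before the arm is displayed, and use that value as the covariate. It cannot depend on the allocation, so the null adjusted odds ratio is 1.00 and the type I error 5%, even when difficult patients go to certified surgeons. Staffing itself stays with the department.
2. Report the actual operator's grade by arm, with changes from plan.
3. Recruitment began in February 2009 (Ethics), so some patients may lack the value. A trial has one confirmatory test, so the model should not differ between subsets of patients. Before database closure, prespecify one model for the whole trial: the planned-grade model if the value is available from before allocation for all patients, otherwise the model without skill. Keep the model with actual skill as a sensitivity analysis.
4. State the target: the model without skill estimates the effect of the assigned strategy, including any staffing difference, and not of technique at equal skill.

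**Cost.** One extra field and a short note to sites; operators are named slightly earlier and later changes documented. If the model without skill becomes primary, any precision gained from the covariate is given up, but the planned 334 never relied on it.

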#### Assessment of the primary endpoint

Bowel obstruction is defined as productive vomiting or the need of gastric tube placement or absolute constipation with a duration of at least three days. This definition is based on the existing trial by Hasegawa [9] which provides the data for sample size calculation of the HASTA-Trial.

Secondary endpoints are the time needed to perform the procedure, wound infection, rate of re-operation due to anastomotic leakage of the ileostomy closure, time to first tolerance to solid food and first bowel movement, whichever of these occurred last, length of postoperative hospital stay, 30 days and 12 months mortality after ileostomy closure, rate of re-operation and re-hospitalization within one year due to bowel obstruction, costs of surgical procedure for the institution (including threads, stapler, time etc.), quality of life (EuroQol 5 D).

Three out of, five visits are documented by the investigator in each center during in hospital phase (screening, intervention and discharge), followed by two telephone interviews for 30 days and 12 months follow up after operation (Table 1 and Figure 2).

**Table 1 T1:** Course of examinations

Visit	1 (=Screening)	2 (Operation)	3 (day of discharge)	4 (30 days post OP)	5 (12 ± 1 months post OP)
Demographics and baseline clinical data	X				

Eligibility criteria	X				

Randomization, Surgical intervention		X			

Clinical visit/Follow-up			X	X	X

Quality of life (EuroQol 5 D)	X			X	X

Safety		X	X	X	X

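### The primary-outcome imputation rule makes no provision for event-free follow-up already documented to discharge, and could overcount bowel obstruction if the full 30-day risk is imputed

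*Protocol article*

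**What the plan says.** The primary endpoint is a single yes/no value: bowel obstruction within 30 days of ileostomy closure. It is observed in two stages. In hospital, the typical symptoms "are detected during regular patient care and documented in the medical record" (Randomization and blinding). The visit schedule reads: "Three out of, five visits are documented by the investigator in each center during in hospital phase (screening, intervention and discharge), followed by two telephone" (Assessment of the primary endpoint); the calls come at 30 days and 12 months. The safety section adds that obstruction is asked for explicitly and entered in the CRF as an endpoint.

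The sample size section expects substantial early loss: "The drop out rate within one month after index operation is expected to be about 20% overall". For these patients the confirmatory analysis gives one rule: "If a patient discontinues from the study prematurely, missing data with respect to the primary outcome variable will be replaced by ICA-r method". A reference follows. The article does not say which risk is imputed, or whether it depends on when or why the patient left.

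**The concern.** The item to be replaced is the 30-day outcome as a whole. Consider two patients who both miss the day-30 call. One obstructed in hospital: the outcome is known to be yes, nothing is missing, and the event counts. The other went home without obstruction: the 30-day outcome is unknown and is replaced. The rule contains nothing that makes the replacement depend on the days already observed without an event.

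If the replacement value is the arm's full 30-day risk, the two patients are treated asymmetrically. Events before loss are used, and event-free time before loss is not. The second patient should carry only the risk remaining after discharge. The observed risk is itself too high in that case, because the patients with a known outcome include lost patients with an early event but no lost patients without one. Both arm rates could then be overstated, by an amount that grows with an arm's drop-out.

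**Working it through.** **Inputs from the protocol.** The Sample size section says the calculations "assume prevalence rates with respect to the primary endpoint of 3% in the stapler group and 14% in the hand-suture group". It gives 133 evaluable patients per group, 20% drop-out and 334 randomized (167 per arm). The values of alpha and power are missing from the text at hand; 5% two-sided and 90% are assumed.

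**The plan's own figure.** With mean rate 0.085:

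n = [1.96·√(2·0.085·0.915) + 1.2816·√(0.14·0.86 + 0.03·0.97)]² / 0.11² = (0.773 + 0.496)² / 0.0121 ≈ 133 per arm.

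133/0.8 = 166.25, rounded up to 167, so 334 in total and 68 more than 266. The stated figures reproduce.

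**Assumptions not in the protocol.** A share s of 30-day events occurs before discharge. Drop-out d falls between discharge and the day-30 call and is unrelated to outcome. Recorded events are kept. All other leavers are imputed at their arm's observed risk.

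**Formulas, for true 30-day risk p.**
- Observed events: p(1−d) + d·p·s
- Patients with known outcome: (1−d) + d·p·s
- Imputed risk, which is also the resulting arm rate: r = first line / second line
- Correct residual risk for a patient event-free at discharge: p(1−s)/(1−p·s)

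**Example, s = 0.7, d = 0.2.**
- Hand-suture: r = (0.112 + 0.0196)/(0.8 + 0.0196) = 0.1316/0.8196 = 16.1%. The residual risk is 0.042/0.902 = 4.7%. About 167·0.2·0.902 = 30 patients are lost event-free; they receive 4.8 events where 1.4 are expected.
- Stapler: r = 0.0282/0.8042 = 3.5%. The residual risk is 0.009/0.979 = 0.9%.

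**Range over s at d = 0.2** (true rates 14% and 3%, true difference 11.0 points, true risk ratio 4.67):

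| s | Hand-suture | Stapler | Relative overcount (hand-suture / stapler) | Difference (points) | Risk ratio |
|---|---|---|---|---|---|
| 0 | 14.0% | 3.0% | 0 / 0% | 11.0 | 4.67 |
| 0.5 | 15.5% | 3.4% | 11 / 12% | 12.1 | 4.60 |
| 0.7 | 16.1% | 3.5% | 15 / 17% | 12.6 | 4.58 |
| 0.9 | 16.6% | 3.7% | 19 / 22% | 13.0 | 4.55 |
| 1 | 16.9% | 3.7% | 21 / 24% | 13.2 | 4.54 |

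**Only half of the leavers seen to discharge, s = 0.7.** Hand-suture: (0.112 + 0.0098)/(0.8 + 0.0098) = 15.0%, a 7% overcount. Stapler: (0.024 + 0.0021)/(0.8 + 0.0021) = 3.25%, an 8% overcount. This is about half the effect.

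**No true difference, p = 0.085 in both arms, s = 0.7.** With equal drop-out, r is the same in both arms, so the expected difference is zero. With 10% versus 30% drop-out: 0.08245/0.90595 = 9.1% versus 0.07735/0.71785 = 10.8%, a spurious 1.7 points. With 15% versus 25%: 9.5% versus 10.3%.

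**Other imputation rules, same assumptions.** Imputing the residual risk returns 14.0% and 3.0%. Imputing no event gives 11.2% and 2.4% at s = 0, rising to 14.0% and 3.0% at s = 1. Re-imputing every leaver at the completers' rate, including those with a recorded event, also leaves 14% and 3%, but overwrites observed primary events.

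**Effect on the test.** In a simulation of 20,000 trials (167 per arm, s = 0.7), full-window replacement gave 16.0% versus 3.5% with a standard error of the difference of 3.52 points. Using follow-up to last contact gave 14.0% versus 3.0% with 3.11 points. The variance is about 22% lower, since (3.11/3.52)² = 0.78. The ratios of difference to standard error are 12.5/3.52 = 3.55 and 11.0/3.11 = 3.54.

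**The case against.** The strongest objection is that the protocol does not say what the overcount requires. It replaces missing data and nowhere states that in-hospital follow-up is set aside or that a patient event-free at discharge gets the full 30-day risk. The method is defined only in a reference that is not at hand, and the direction of any bias depends on it. This stands. A reader might infer that obstruction will certainly be overcounted in both arms; the document does not support that.

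The size also rests on figures the protocol does not give. No split of events before and after discharge is stated, and at s = 0 the bias vanishes. The 20% is set against this requirement: "a sample size of n = 133 evaluable patients (treatment and follow up according to the protocol) per group is necessary". It may therefore include treatment deviators whose outcome is known. Patients are randomized the day before or on the day of surgery, so some leavers may have no postoperative observation at all. The 10% versus 30% split is an illustration; the plan gives only an overall rate. These points stand too, which is why ranges are shown.

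A reader might also infer that the lower variance buys power. It does not: the ratio of difference to standard error is about 3.5 either way.

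Finally, such detail may belong to the SAP, which is not shown. That holds in part. However, the article itself commits the confirmatory test to a named replacement method, and none of the whole-window readings examined above uses the recorded event-free time. The point is therefore about how that commitment is worded; it does not rest on the absence of SAP detail.

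**Conclusion.** The concern holds conditionally. The rule makes no provision for event-free follow-up documented to discharge. If early events are kept and event-free leavers receive the arm's full observed 30-day risk, the primary event rates are overstated by 0% to about 21–24% in relative terms at 20% drop-out. The figure is roughly 15–17% if 70% of events precede discharge, and about half of that if only half of the leavers are seen to discharge. All of this assumes drop-out after discharge that is unrelated to outcome.

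The harm is mainly to the reported rates and their absolute difference. The risk ratio moves from 4.67 to 4.54 at most. A spurious difference in expectation needs unequal drop-out, which is possible because neither patients nor surgeons are blinded; the 1.7 points in the illustration are roughly half a standard error at this sample size. The change is worth making because it is cheap and uses data already collected, but no error in the confirmatory test has been demonstrated.

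**What to change.** First check which risk the cited method assigns. Then reword the missing-data rule under Confirmatory analysis, and carry it into the SAP before database closure, along these lines:

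- An obstruction recorded up to the last documented contact counts as an event.
- For a patient event-free at that contact, only the remaining days to day 30 are missing. They are multiply imputed within arm, using the risk of a first obstruction between that day and day 30 among patients event-free at that day.
- Patients with no postoperative observation are imputed over the full 30 days.
- The completed data are analysed in the planned logistic model with intervention and skill of surgeon.
- ICA-r is kept as a sensitivity analysis.

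Comparing Kaplan-Meier day-30 risks would not be an equivalent substitute, because it would replace the planned logistic model adjusted for surgeon skill.

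The cost is wording and modest programming. The rule needs the dates of event and of last contact, with no added visits or patients. Its weakness is the assumption that, among patients event-free at last contact, those lost have the same later risk as those followed; the retained ICA-r analysis examines sensitivity to this.
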